## Abstract

**Background:**

Traditionally, cerebellar disorders including ataxias have been associated with deficits in motor control and motor learning. Since the 1980’s growing evidence has emerged that cerebellar diseases also impede cognitive and affective processes such as executive and linguistic functions, visuospatial abilities and regulation of emotion and affect. This combination of non-motor symptoms has been named *Cerebellar Cognitive Affective/ Schmahmann Syndrome (CCAS)*. To date, diagnosis relies on non-standardized bedside cognitive examination and, if available, detailed neuropsychological test batteries. Recently, a short and easy applicable bedside test (CCAS Scale) has been developed to screen for CCAS. It has been validated in an US-American cohort of adults with cerebellar disorders and healthy controls. As yet, the CCAS Scale has only been available in American English. We present a German version of the scale and the study protocol of its ongoing validation in a German-speaking patient cohort.

**Methods:**

A preliminary German version has been created from the original CCAS Scale using a standardized translation procedure. This version has been pre-tested in cerebellar patients and healthy controls including medical experts and laypersons to ensure that instructions are well understandable, and that no information has been lost or added during translation. This preliminary German version will be validated in a minimum of 65 patients with cerebellar disease and 65 matched healthy controls. We test whether selectivity and sensitivity of the German CCAS Scale is comparable to the original CCAS Scale using the same cut-off values for each of the test items, and the same pass/ fail criteria to determine the presence of CCAS. Furthermore, internal consistency, test-retest and interrater reliability will be evaluated. In addition, construct validity will be tested in a subset of patients and controls in whom detailed neuropsychological testing will be available. Secondary aims will be examination of possible correlations between clinical features (e.g. disease duration, clinical ataxia scores) and CCAS scores.

**Perspective:**

The overall aim is to deliver a validated bedside test to screen for CCAS in German-speaking patients which can also be used in future natural history and therapeutic trials.

**Study registration:**

The study is registered at the German Clinical Study Register (DRKS-ID: DRKS00016854).

## Background

Cerebellar disease results in well-known motor performance deficits, including ataxia of stance and gait, limb incoordination, dysarthria, and oculomotor abnormalities. During the last decades, there has been growing evidence that cerebellar disease is not only accompanied by motor disturbances but also by cognitive and affective symptoms (see [1–3] for reviews). As early as 1998, Schmahmann and Sherman introduced the *Cerebellar Cognitive Affective/ Schmahmann Syndrome (CCAS)* [4]*.* The core symptoms of CCAS are difficulties with executive, linguistic and visuospatial functions as well as problems with the regulation of emotion and affect. Since its original description, evidence for the presence of CCAS has been accumulating in pediatric and adult patients suffering from different cerebellar diseases including various hereditary ataxias, cerebellar tumors, and cerebellar stroke [1–3]. In recent years, advances in structural and functional brain imaging allowed for detailed mapping of cognitive functions in the posterolateral cerebellar hemisphere [5–9]. As yet, diagnosis of CCAS relies on non-standardized bedside cognitive examination and, if available, detailed neuropsychological test batteries. Until recently, there has not been a validated bedside test that was able to reliably screen for CCAS in cerebellar patients – unlike well-established bedside tests for dementias or mild cognitive impairment (MCI), i.e. Mini Mental State Examination (MMSE) or Montreal Cognitive Assessment (MoCA). However, MMSE and MoCA are of limited use to screen for CCAS because cerebellar patients frequently perform within the normal range [10]. Recently, Schmahmann and colleagues [10] have developed a bedside test designed to screen for CCAS in adults. In order to develop this CCAS Scale, they first applied a broad battery of 36 well-established neuropsychological tests in a large group of cerebellar patients primarily suffering from cerebellar degeneration. In the novel CCAS Scale, tests were implemented which captured the core cognitive domains of CCAS, distinguished best between cerebellar patients and controls, and at the same time were short and easy enough to be applied in a bedside setting. These include test items for semantic and phonemic fluency, category switching, verbal registration and delayed verbal recall, digit span forward and backward, cube draw and copy, similarities, go/ no-go, and affect. Single tests can either be passed reaching a specific cut-off score or failed. CCAS is considered possible if one test is failed, probable if two tests are failed, and definite if three or more tests are failed. Version A of the CCAS Scale has then been validated in another US-American cohort of 39 adult cerebellar patients, including patients with cerebellar degeneration and focal cerebellar lesions and 55 matched healthy controls. It exhibited high values for selectivity [that is the ability to distinguish between patients and controls, or in other words preventing controls from being diagnosed as patients; possible/ probable/ definite CCAS: 78/ 93/ 100%] and reasonable sensitivity [that is the probability that a patient is identified as a patient; possible/ probable/ definite CCAS: 95/ 82/ 46%]. Furthermore, it showed modest internal consistency using Cronbach’s alpha value (= 0.59) indicating that no test item within the scale measures the exact same domain(s) as another item. Thus, no test item is redundant. Comparing patients with pure cerebellar lesions and patients with additional extracerebellar involvement the authors found that difficulties in verbal registration and delayed verbal recall were more prominent in the latter. Therefore, poor performance in these two test items is indicative of extracerebellar involvement (“red flag”). In addition to the pass/ fail criteria which are used to screen for CCAS, a total sum score is calculated which allows for follow-up examinations in individual patients [10]. Three parallel versions B-D were developed to enable repeated assessments. In the present study preliminary German versions of the CCAS Scale are introduced, and the study protocol for their validation is presented.

## Methods

### Study aims

The first primary aim of this study was to create preliminary German versions of the CCAS Scale. The second primary aim will be their validation in a large cohort of patients with various cerebellar disorders and healthy age-, sex-, and education-matched controls. Secondary aims will be to examine possible relationships between clinical features such as disease duration or severity of cerebellar motor symptoms, and the CCAS score.

### Study description and study design

#### Translation process of the original CCAS Scale into German language

A group of medical experts translated the original American English versions A-D of the CCAS Scale into German accounting for language- (and cultural-) dependent differences while staying as close as possible to the original CCAS Scale. A standardized, six step procedure was used following guidelines for cross-cultural translation, adaptation, and validation of self-report measures, instruments, or scales for use in healthcare research [11, 12]. The expert group comprised three independent teams each consisting of two individuals (team 1: University Hospital and German Center for Neurodegenerative Diseases Bonn: [name] = neuropsychologist, [name] = neurologist; team 2: University Hospital Essen: [name], [name] = neurologists; team 3: University Hospital Tuebingen: [name] = neuropsychologist, [name] = neurologist).

*Step 1:* Each team translated the original CCAS Scales (A-D) independently to German. *Step 2:* For each version (A-D) a consensus version was derived. *Step 3:* Consensus version A was then translated back to American English by a bilingual expert ([name] = neuroscientist). The parallel versions B-D were not translated back because instructions on the test form were similar in all versions. *Step 4:* Discrepancies were resolved in a joined discussion and a German prototype version A was formed. The senior author ([name]) of the original CCAS Scale was involved in this step (and step 6, see below) to ensure that no information has been lost or added during the translation process. *Step 5:* The prototype version A was pretested in a small cohort of medical experts and laypersons. The medical expert group consisted of eleven neurologists, three neuropsychologists and one medical student (mean age: 33.8 ± 6.4 yrs.; age range: 23.8–49.0 yrs.; 6 males, 9 females; mean education: 19.6 ± 1.2 yrs.). None of them was involved in steps 1–4. The lay group consisted of 12 cerebellar patients, one healthy subject and three healthy first-degree relatives of patients with hereditary ataxias, i.e. persons at risk (mean age: 59.5 ± 14.9; age range: 23.4–84.0 yrs.; 8 males, 7 females; mean education: 15.2 ± 4.2 yrs.). All participants were asked to rate each item of the German prototype version A as *“easy to understand”*, *“comprehensible”*, *“difficult to understand”*, *or “incomprehensible”*. *Step 6:* Imprecise and misleading items were revised (for details see Supplementary Materials, Part 2). The resulting preliminary version of the CCAS Scale, Version A, is shown in Fig. 1. The parallel versions were revised accordingly and are shown in Supplementary Materials, Part 3.

**Fig. 1 Fig1:**
[figure not shown]

[figure not shown]

[figure not shown]

[figure not shown]
Preliminary German CCAS Scale, Version A

There are also detailed test instructions for the examiner. Firstly, these instructions have been translated independently by each team, and next a consensus was derived (see Supplementary Materials, Part 4).

#### Validation process

##### Inclusion and exclusion criteria

To be eligible for the study, subjects must be 18 years or older, German-speaking (primary language) and they must be able to understand and follow instructions and to give informed consent. Exclusion criteria comprise neurological or psychiatric disorders in control participants, and neurological disease other than cerebellar disease and primary psychiatric disorders in patients. Patients will be included who suffer from degenerative cerebellar disorders or focal cerebellar lesions (e.g. cerebellar stroke, tumor, or cerebellar surgical lesions). Alcohol or drug abuse, intake of centrally acting drugs (other than low dose antidepressants) and consuming diseases or general poor health are further exclusion criteria for all participants. Furthermore, participants under legal supervision will not be recruited. For detailed in- and exclusion criteria see Table 1.

**Table 1 Tab1:** Inclusion and exclusion criteria for patient and control selection

Group	Inclusion criteria	Exclusion criteria
**General**	- Age ≥ 18 years - German-speaking (primary language) - Informed consent	- Alcohol or drug abuse - Intake of centrally acting drugs (other than low-dose antidepressants) - Consuming diseases - Poor health condition - Persons under legal supervision
**Patients**	- General inclusion criteria	- General exclusion criteria - Severe primary psychiatric disorders
**Degenerative Cerebellar Disorders**		
**Cer-pure** Disorders primarily affecting the cerebellum	- SAOA - EA1 and EA2 - SCA6 - SCA8 - SCA14 - ANO10 - Post-inflammatory cerebellar degeneration	
**Cer-plus** Disorders with relevant extracerebellar involvement	- MSA-C - all other hereditary ataxias including: SCA1, 2, 3, Friedreich’s ataxia, early onset cerebellar ataxias	
**Focal Cerebellar Lesions**		
**Cer-pure/ cer-plus**	- Cerebellar stroke - Cerebellar hemorrhage - Cerebellar tumor - Cerebellar surgical lesion	
**Controls**	- General inclusion criteria	- General exclusion criteria - Neurological and psychiatric disorders
**Pretesting Subjects**	- General inclusion criteria	- General exclusion criteria - Neurologists and psychologists that were involved in the development of the German CCAS Scales

*Abbreviations*: *Cer-pure* Isolated Cerebellar Disease/ Lesion, *Cer-plus* Cerebellar Plus Disease/ Lesion, *SAOA* Sporadic Adult Onset Ataxia, *EA1* Episodic Ataxia Type 1, *EA2* Episodic Ataxia Type 2, *SCA1, 2, 3, 6, 8, 14* Spinocerebellar Ataxia Type 1, 2, 3, 6, 8, 14, *ANO10* Spinocerebellar Ataxia, Autosomal-Recessive Type 10, *MSA-C* Multisystem Atrophy Cerebellar Type, *CCAS* Cerebellar Cognitive Affective/ Schmahmann Syndrome

##### Study sample

For validation of version A at least 65 patients and an equal number of matched healthy controls will be recruited. About one third (≥ 25) of the patients will suffer from disorders that primarily affect the cerebellum (isolated cerebellar disease = cer-pure: 1. degenerative cerebellar disorders, e.g. spinocerebellar ataxia type 6 (SCA6); 2. focal cerebellar lesions, e.g. cerebellar stroke). The other two thirds (≥ 40 patients) will suffer from disorders with additional extracerebellar involvement (cerebellar plus disease = cer-plus: 1. degenerative cerebellar disorders, e.g. SCA1, 2 or 3; 2. focal cerebellar lesions, e.g. cerebellar stroke with additional involvement of the brain stem). Group assignment in patients with cerebellar degeneration goes by diagnosis: A genetic disease, which is known to involve extracerebellar regions, is considered a “cer-plus form”, although the clinical phenotype at the time of testing may be pure cerebellar.

An equivalent number of healthy matched participants will serve as controls. Each patient will be matched with a control participant of same sex, similar age (interval: +/− 5 years) and similar years of education (intervals: < 9 yrs., 9–10 yrs., 11–13 yrs., 14–16 yrs., > 16 yrs.). We will use the same matching criteria as in [10] except for education matching because of the different educational systems in Germany and the United States.

Parallel versions B-D will be validated in groups of 25 patients (cer-pure and cer-plus, respectively) and 25 matched healthy controls each.

Patients in this investigator-initiated, multicenter study will be recruited from the ataxia clinics at the Departments of Neurology of the University Hospitals in Aachen, Bonn, Duesseldorf, Essen, Heidelberg and Tuebingen, as well as from the MediClin Fachklinik Rhein-Ruhr in Essen, and the Departments of Neurosurgery of the University Hospital in Essen and at the Klinikum Dortmund. Essen is the coordinating site. Furthermore, we will collaborate with the “Deutsche Heredo-Ataxie Gesellschaft e.V. (DHAG)”, a patient support group, and patients will be recruited via their newsletter and webpage. Healthy controls will be recruited from patients’ families and by public bulletins.

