##### Demographics and clinical assessment of cerebellar motor syndrome

Demographics including years of education and employment, educational achievements as well as occupational and marital status will be recorded. For patients, medical records and available brain scans will be evaluated. Age of onset, disease duration and in case of genetically proven nucleotide repeat diseases the repeat length will be documented. Furthermore, a detailed medical history will be taken, and a neurological examination will be performed in every participant. Severity of cerebellar ataxia in patients will be evaluated using different clinical ataxia scales: The Scale for the Assessment and Rating of Ataxia (SARA) [13] will be used because of its widespread use. In addition, the International Cooperative Ataxia Rating Scale (ICARS) [14] will be used because it includes rating of cerebellar oculomotor deficits. Its short form – BARS – [15] will be used to enable direct comparison with the original US-American validation study. The SpinoCerebellar Ataxia Functional Index (SCAFI) [16] will be assessed because it allows for a more objective quantification of motor deficits. Finally, non-ataxia signs will be assessed semi-quantitatively using the Inventory of Non-Ataxia Signs (INAS) [17].

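### The control criteria admit first-degree relatives of patients with hereditary ataxia, whom the article itself calls at risk; this may bias selectivity downward

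*Protocol article*

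**What the plan says.** Study sample names two sources of controls: "Healthy controls will be recruited from patients’ families and by public bulletins". Nothing there limits family members to those unrelated by blood. The same section sets the matching: "Each patient will be matched with a control participant of same sex, similar age" (within 5 years), and similar education.

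Inclusion and exclusion criteria states: "Exclusion criteria comprise neurological or psychiatric disorders in control participants". It then refers the reader onward: "For detailed in- and exclusion criteria see Table 1". In Table 1 the Controls row adds one exclusion to the general ones: "Neurological and psychiatric disorders". Neither place mentions blood relationship or carrier status.

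Table 1 admits many hereditary diseases among patients. SCA1, 2 and 3, Friedreich's ataxia and other hereditary ataxias are in the cer-plus group; EA1, EA2, SCA6, SCA8, SCA14 and ANO10 are in the cer-pure group.

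In Step 5 of the translation process, the lay pretest group contained, besides 12 patients, "one healthy subject and three healthy first-degree relatives of patients with hereditary ataxias, i.e. persons at risk".

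On screening, Demographics and clinical assessment says that "a detailed medical history will be taken, and a neurological examination will be performed in every participant". Repeat length is listed with the patient data; no genetic criterion for controls is mentioned.

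Data analysis defines selectivity as the percentage of controls correctly identified as controls. It provides for adjusting item or CCAS cut-offs if results fall below those of the original scale. Perspective names high selectivity as the primary aim.

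**The concern.** The article separates at-risk relatives from the healthy subject when it describes the pretest, but does not carry that distinction into the control criteria for the validation. A relative who carries the family mutation and has no manifest disease satisfies every listed control criterion. If that person already has subtle cognitive deficits and fails items, the analysis counts a false positive, although the scale may have detected early cerebellar disease.

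The control group is the whole denominator of selectivity, so any such contamination enters the primary estimate directly. It could also affect the scale itself. Control failures that pull selectivity below the original values could prompt cut-offs that are easier to pass, and these would then detect fewer patients.

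**Working it through.** **No figure to reproduce.** The article gives no count of relatives among controls and no sample-size derivation. The check is therefore a bias model with stated assumptions.

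**Inputs from the article**
- Controls for version A: at least 65 (Study sample).
- Original scale, possible / probable / definite CCAS (Background): selectivity 78 / 93 / 100% in 55 controls; sensitivity 95 / 82 / 46% in 39 patients. These are attainable counts: 43, 51 and 55 of 55; 37, 32 and 18 of 39.

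**Assumptions, none from the article**
- r = share of controls who are first-degree relatives of patients with hereditary ataxia: 20%.
- c = probability that such a relative is a carrier: 25 to 50% before screening.
- m = share of carriers already manifest and removed by history and examination: 0, 50 or 80%.
- h = carriers' excess failure as a fraction of the patient-control gap: 0.5 (0 = like controls, 1 = like patients).

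**Formulas**
- Carrier probability after screening: c' = c(1 − m) / [c(1 − m) + (1 − c)].
- Expected loss of selectivity: r × c' × h × [Sp − (1 − Se)].

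The gap Sp − (1 − Se) is 0.78 − 0.05 = 0.73 (possible), 0.93 − 0.18 = 0.75 (probable) and 1.00 − 0.54 = 0.46 (definite). With h = 0.5, each carrier costs 0.365, 0.375 and 0.23.

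**Results for probable CCAS (r = 20%, h = 0.5)**

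| c | m | c' | r × c' | Loss (points) | Expected selectivity |
|---|---|---|---|---|---|
| 50% | 0 | 50.0% | 10.0% | 3.75 | 89.2% |
| 50% | 50% | 33.3% | 6.7% | 2.5 | 90.5% |
| 50% | 80% | 16.7% | 3.3% | 1.25 | 91.8% |
| 25% | 0 | 25.0% | 5.0% | 1.9 | 91.1% |
| 25% | 50% | 14.3% | 2.9% | 1.1 | 91.9% |
| 25% | 80% | 6.25% | 1.25% | 0.5 | 92.5% |

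Over the same rows, the loss runs from 0.0125 × 0.365 = 0.5 to 0.10 × 0.365 = 3.7 points for possible CCAS, and from 0.0125 × 0.23 = 0.3 to 0.10 × 0.23 = 2.3 points for definite CCAS.

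**Sensitivity to the assumptions.** If h = 0 the loss is zero for any r and c. With r = 10%, c = 25%, m = 0 and h = 0.5, it is 0.10 × 0.25 × 0.375 = 0.9 points for probable CCAS. With r = 25%, c = 50%, m = 0 and h = 0.5, it is 0.25 × 0.50 × 0.375 = 4.7 points.

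**Against sampling error.** The standard error for probable CCAS at n = 65 is √(0.93 × 0.07 / 65) = 3.2 points.

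**Against the adjustment rule.** Observed selectivity for probable CCAS is below 93% when at most 60 of 65 controls pass, since 0.93 × 65 = 60.45. With X ~ Binomial(65, p), P(X ≤ 60) is 48% at p = 0.93, 54% at p = 0.925 (smallest loss in the table) and 84% at p = 0.8925 (largest loss). A shortfall is therefore about as likely as not without any carriers, and contamination of this size makes it more likely.

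**The case against.** The strongest reply is that the article does not show any bias. Bias requires that at-risk relatives are enrolled, that some are carriers, and that carriers with a normal neurological examination still fail more items. The article establishes none of these and says nothing about cognition in pre-manifest carriers. This stands. A reader might infer that the primary estimate is biased downward as a matter of fact; the text supports only that it may be.

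Several further points limit the concern.
- A reader might infer from the matching rule that siblings will be the usual family controls. The article does not say that a patient is matched to his or her own relative. Spouses and in-laws can be matched to other patients, bulletins are a second source, and several eligible conditions (stroke, hemorrhage, tumor, surgical lesions, post-inflammatory degeneration) raise no such question. The 20% share is an assumption only.
- The history and neurological examination remove manifest carriers. Where relatives are close in age to an affected patient, this screen may remove many, which is why the working includes m = 50% and 80%.
- Over most of the range the loss is smaller than one standard error; only at the top (3.75 against 3.2 points) does it slightly exceed it.
- The definite criterion invites an alarming figure. At carrier shares of 5 to 10% of controls, the chance of at least one definite false positive among 65 is 1 − 0.9885^65 = 53% to 1 − 0.977^65 = 78%. That takes true selectivity to be exactly 100%, on the strength of 55 of 55 controls, for which the one-sided 95% lower limit is 0.05^(1/55) = 94.7%. With no carriers at all, the chance is 1 − 0.99^65 = 48% at a true 99% and 73% at 98%. It should not be read as evidence of contamination.
- Lower detection of patients is a further step. Data analysis says individual tests are examined first and that adjustment aims at reasonable sensitivity as well.

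These points reduce certainty and size. They do not close the gap in the criteria, which appear in a table that the article presents as the detailed list. A loss near the sampling error would also be hard to recognise afterwards, which favours prevention by design.

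**Conclusion.** The point holds conditionally. The stated control criteria allow people whom the article elsewhere calls at risk into the group from which the primary selectivity estimate is calculated. Any bias from carriers who fail more items would be downward, and it could contribute to a cut-off change.

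The article does not give the size. It is zero if carriers perform like controls. For probable CCAS it is about 0.5 to 4 points if 20% of controls are such relatives, 25 to 50% of those relatives are carriers before screening, up to 80% of carriers are removed as manifest, and the rest fail halfway between control and patient rates. All four inputs are assumptions. The correction is worth making because it is cheap and protects the primary estimate, although no bias has been demonstrated.

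**What to change.** In Table 1, Controls row, add an exclusion for first-degree blood relatives of patients with hereditary ataxia. Spouses, in-laws, relatives of patients with focal or non-hereditary disease, and bulletin volunteers remain eligible. The exclusion goes no further than the group the article itself names as at risk, and it needs no genetic testing.

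If such relatives are already enrolled, record each control's kinship to a patient and that patient's diagnosis. Report selectivity with and without these relatives, and base any cut-off adjustment on the analysis without them.

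The cost is one line in the eligibility table and slightly slower control recruitment. If relatives are already in the sample, it is a slightly smaller control set in the restricted analysis.
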